## Abstract

**Background:**

The traditional management of papillary thyroid cancer (PTC) is thyroidectomy (total or partial removal of the thyroid). Active surveillance (AS) may be considered as an alternative option for small, low risk PTC. AS involves close follow-up (including regularly scheduled clinical and radiological assessments), with the intention of intervening with surgery for disease progression or patient preference.

**Methods:**

This is a protocol for a prospective, observational, long-term follow-up multi-centre Canadian cohort study. Consenting eligible adults with small, low risk PTC (< 2cm in maximal diameter, confined to the thyroid, and not immediately adjacent to critical structures in the neck) are offered the choice of AS or surgery for management of PTC. Patient participants are free to choose either option (AS or surgery) and the disease management course is thus not assigned by the investigators. Surgery is provided as usual care by a surgeon in an institution of the patient’s choice. Our primary objective is to determine the rate of ‘failure’ of disease management in respective AS and surgical arms as defined by: i) AS arm – surgery for progression of PTC, and ii) surgical arm - surgery or other treatment for disease persistence or progression after completing initial treatment. Secondary outcomes include long-term thyroid oncologic and treatment outcomes, as well as patient-reported outcomes.

**Discussion:**

The results from this study will provide long-term clinical and patient reported outcome evidence regarding active surveillance or immediate surgery for management of small, low risk PTC. This will inform future clinical trials in disease management of small, low risk papillary thyroid cancer.

**Registration details:**

This prospective observational cohort study is registered on clinicaltrials.gov (NCT04624477), but it should not be considered a clinical trial as there is no assigned intervention and patients are free to choose either AS or surgery.

## Introduction

Over the last three decades, the incidence rate of thyroid cancer (TC) has been rising in Canada (1), yet the disease-related mortality rate has remained very low (1, 2). Globally, this trend has been partly explained by overdiagnosis of TC - particularly low risk disease, with an associated low risk of disease-related mortality (3). In Canada, small papillary thyroid cancers (PTCs) have been increasingly diagnosed (4). The traditional standard of care in initial PTC management has been thyroidectomy (total or partial thyroid removal by surgery) and this may be followed by thyroid hormone treatment and sometimes radioactive iodine treatment (5). However, recently the authors of the American Association of Endocrine Surgeons’ Clinical Practice Guidelines for Definitive Surgical Management of Thyroid Diseases in Adults have indicated that “an active surveillance protocol for papillary thyroid microcarcinoma may be appropriate for carefully selected, informed, and compliant patients” (6). AS has also been discussed in the American Thyroid Association (ATA) guidelines on management of differentiated thyroid cancer in adults (5). Active surveillance (AS) is defined by close clinical follow-up instead of immediate surgery, including regularly scheduled neck ultrasound imaging, with the intention for surgery (with curative intent) if there is evidence of disease progression while under observation or if the patient requests surgery for another reason. Offering the option of AS to patients with small, low risk PTC may mitigate the risk of treatment-related morbidity for disease that may ultimately never progress, yet still allow for curative treatment if early progression is detected in the surveillance process.

Recent literature suggests that AS of small, low risk PTC (confined to the thyroid), is safe (7). In a recent systematic review and meta-analysis of long-term outcomes of patients with small, low risk PTC under AS, Cho et al. reported that only 5.3% of patients experienced tumor growth ≥3 mm in maximal diameter and 1.6% of patients developed nodal metastases during 5 years of follow-up (7). No thyroid cancer-related deaths nor incident distant metastases have been observed in patients with small, low risk PTC under AS (8). However, most of the published literature on AS includes primarily patients with papillary microcarcinoma (PTC 1cm or smaller in largest diameter) (7), which may not routinely necessitate biopsy, per recent ATA clinical practice guidelines guidance (5). In 2016, in Toronto, we initiated a multi-phase prospective observational study of patients with small, low risk PTC < 2cm in maximal diameter (i.e. including PTC larger than microcarcinoma), which we refer to as very low risk PTC (VL-PTC) (9). In the Toronto study, we offer patients a choice of surgery or AS and report their disease management decision (decision-making phase of the study) (9). We also prospectively report patient outcomes in patients choosing AS or surgery (Clinicaltrials.gov: NCT03271892) (9). An interim analysis on the disease management decisions of the first 100 patients enrolled in the Toronto study was recently published (10). About half of the enrolled patients in the Toronto study have a PTC larger than a microcarcinoma (10). We reported that 71.0% (71/100) of our patients chose AS over surgery and patients’ rationale for the decision was described in detail using a qualitative approach (10). Although the high percentage selecting AS may in part reflect some referral bias (both self-referral of patients who are interested in AS and referral from thyroid cancer specialists whose patients specifically request AS), these preliminary data suggest that among Canadians with VL-PTC there is substantial interest in being offered the choice of AS as an alternative to surgery (10). One of the main reasons why our patients chose AS, was a desire to avoid immediate thyroid surgery, with the potential implications of thyroid hormone treatment (10). In contrast, patients who chose surgery wanted to remove any thyroid cancer in their body (i.e. aspired for cure of the disease). Recruitment in the Toronto prospective, observational AS decision-making study is now complete (200 patients), (with a full report on disease management decisions forthcoming). Furthermore, long-term patient follow-up is ongoing in the Toronto study. In response to a) popularity of the option of AS in patients with small, low risk PTC in the Toronto study (10), b) recently acquired knowledge in this area (in the published literature and clinical practice guidelines), and c) recent interest among Canadian thyroid cancer specialists, we have developed a prospective observational pan-Canadian study examining long-term clinical and patient-reported outcomes on AS and surgery for VL-PTC. The proposed study, described below, is similar to design to the original Toronto study, but with a focus on clinical outcomes and patient reported outcomes over a long period of follow-up.

## Materials and Methods

### Study Design and Setting

We plan a multi-centre prospective observational cohort study to examine long-term outcomes of patients with small, low risk PTC, confined to the thyroid, who have made an initial choice of AS or surgery. A draft of this study protocol was presented at a national investigator meeting held in Toronto on November 30, 2019 (sponsored by a Canadian Institutes of Health Research (CIHR) planning grant) (11) and the protocol was then refined, based on feedback from the investigators at the meeting. The nine planned participating institutions include: University Health Network/University of Toronto (Toronto, Ontario), Centre Hospitalier de l’Université de Montréal (Montreal, Quebec), Dalhousie University (Halifax, Nova Scotia), Université Laval (Quebec City, Quebec), McMaster University (Hamilton, Ontario), University of British Columbia (Vancouver, British Columbia), University of Calgary (Calgary, Alberta), University of Ottawa (Ottawa, Ontario), and Western University (London, Ontario).

### Study Aim and Primary Outcomes

Our primary research objective is to quantify the safety of AS relative to immediate surgery, by examining the rate of ‘failure’ of disease management over the period of follow-up in VL-PTC patients choosing AS and those choosing surgery. ‘Failure’ of disease management is defined as follows in each arm of the study: i) AS arm – thyroid surgery for progression of cancer, and ii) Surgical arm - surgery or other thyroid cancer treatments for structural disease recurrence or persistence at any time point after completion of initial treatment. Treatment of recurrent or persistent thyroid cancer (after completion of initial treatment) may include additional surgery, radioactive iodine treatment, ethanol ablation of lymph nodes, or external beam radiation treatment. Data will be reported separately for each arm.

### The Study Population Eligibility Criteria and Recruitment

Consenting adults (age ≥18 years) with surgically untreated PTC < 2cm in maximal diameter that is confined to the thyroid, not encroaching on critical structures in the neck (e.g. trachea or recurrent laryngeal nerve), with no evidence of extrathyroidal extension nor nodal metastases (which we refer to as very low risk PTC, VL-PTC), are eligible for inclusion in the study (**Table 1**). Several minor changes in the original Toronto inclusion and exclusion criteria are also detailed in **Table 1**, largely enabling recruitment of interested patient groups (such as those with other low risk malignancies or other thyroid or parathyroid disease for which there is no absolute indication for surgery– see **Table 1**). Data from patients who consented to long-term follow-up in the original Toronto study (NCT03271892) will be reported with data from the additional patients recruited in the multi-centre study (NCT04624477).

**Table 1 T1:** Eligibility criteria.

Participant Inclusion and Exclusion Criteria	
*Inclusion criteria*	*Exclusion criteria*
•Age 18 years or older	•Thyroid cancer that is known to have extended beyond the thyroid (e.g. extrathyroidal extension, nodal or distant metastases)
•Newly diagnosed, untreated papillary thyroid cancer (PTC) < 2cm in maximal diameter on ultrasound imaging. The fine needle aspiration biopsy cytology of the primary tumor is required to be read as PTC or suspicious for PTC*	•A history of prior thyroid surgery*
•Absence of metastatic cervical lymphadenopathy on imaging (ultrasound the neck or other)	•The primary PTC is encroaching the recurrent laryngeal nerve or trachea (which is considered at potential high risk for invading these structures in the event of disease progression)
•No other absolute* indication for thyroid or parathyroid surgery at the time of the assessment	•Proven or suspected poorly differentiated or non-papillary thyroid cancer
•Patient must grant permission for review of thyroid cancer-related medical records	Medically unfit for surgery due to severe co-morbidity. Severe comorbidity may include another active malignancy with limited life expectancy of < 1 year*
	•Pregnancy at the time of study enrollment
	•One or more absolute indications for thyroid or parathyroid surgery (other than thyroid cancer)*
	•Patient is unable or unwilling to consent for study follow-up procedures (e.g. due to current severe active cognitive or psychiatric impairment, substance abuse, or other reasons)

*****Changes in the original Toronto protocol, approved by the University Health Network Research Ethics Board (April 7, 2020) and incorporated in the pan-Canadian at onset of the study include: not mandating central cytopathology review (i.e. may be performed at the discretion of the investigator if there is any uncertainty or concern about the original review, but not mandating this due to limited value with some patient delays observed in the Toronto study), not excluding patients who have mild thyroid or parathyroid disease that does not meet established absolute indications for surgical treatment (e.g. hyperthyroidism under control with medication, mild primary hyperparathyroidism), excluding patients with any prior thyroid surgery (not just thyroid cancer surgery, as prior partial thyroidectomy could confound results at long-term follow-up, although no patients with prior thyroid surgery have been enrolled in the Toronto study), and permitting patients who have had a recent diagnosis, treatment, or active surveillance of another malignancy to participate in the study if the expected survival of the other malignancy is > 1 year (as patients with other malignancies, including those under active surveillance for other low risk cancers, have expressed interest in this study).

Patient recruitment at all study sites is focused in participating thyroid cancer clinics, although eligible patients may be referred by healthcare providers or refer themselves by contacting a study centre. Screening for eligibility in consenting patients is performed by a research assistant, under the supervision of a site investigator. All patients are required to have at least one consultation by a thyroid cancer surgeon (at any institution) such that the type of surgery that would be recommended for the particular case, as well as potential complications, are explained in detail (as per usual clinical practice of the surgeon). Participants are informed about the options of AS and surgery and provided written handout summarizing the relevant literature on both AS and surgical options, and given the opportunity to meet with a study physician to discuss the provided information and obtain answers to any related questions. Patients are free to make their own disease management choice and the clinical disease management course (i.e. surgery or AS) is not assigned by the investigators in the study. Baseline neck imaging studies are reviewed by a study investigator experienced in interpretation of neck ultrasound or a radiologist with expertise in ultrasound who is familiar with the study, to confirm eligibility. Training on evaluation of ultrasounds for baseline assessment and follow-up has been provided at a national investigator meeting ([name], [name]) and will be revisited during the course of the study at yearly (or more frequent) investigator meetings. The central study co-primary investigators ([name], [name]) are available to advise and support the other investigators throughout the study. A REDCap database has been developed by the THETA Group at University Health Network, for centralized electronic collection of data entered by research staff at each study site.

### Study Follow-Up Assessments and Outcomes

As in the original study (9), AS routine follow-up includes clinical assessment (comprised of neck ultrasound at the participating institution, bloodwork (TSH, thyroglobulin, thyroglobulin antibody), and investigator clinical evaluation) every 6 months for two years, then yearly if there has been no evidence of disease progression. More frequent assessments or additional investigations may be performed if there is a clinical concern. Indefinite clinical follow-up at a participating study site is offered for patients as long as they are undergoing AS. The criteria for recommending surgery for disease progression (the same as in the original study) are defined as any of: 1) primary tumor growth > 3mm (in largest diameter, confirmed on two consecutive ultrasound exams); 2) PTC growth in a location that is concerning (i.e. encroaching the trachea or course of the recurrent laryngeal nerve or grossly invading extrathyroidal tissues); or 3) incident nodal metastatic disease, or 4) incident distant metastatic disease (**Table 2**) (9). Furthermore, as in the original Toronto study, patients under AS are free to choose to cross over to surgery in the absence of disease progression at any point in follow-up and may continue to be followed in the study (in a manner analogous to that of patients who choose immediate surgery) (9). In patients initially choosing surgery or crossing over from AS to surgery, the extent of surgery and any other treatments will be at the discretion of the treating surgeon or thyroid cancer specialists (who are not mandated to be at a participating study site), and is intended to reflect usual care. Typical post-surgical disease surveillance of patients treated for VL-PTC includes periodic clinical evaluations, neck ultrasounds, and bloodwork (TSH, thyroglobulin, thyroglobulin antibody), with additional investigations considered depending on the clinical circumstance. In the event that the clinical criteria for salvage surgery are met, it is expected that the treating or referring surgeon will perform thyroid surgery, but the patient may opt for a surgeon of her or his choice at any institution (usual care). Although highly unlikely, it is possible that a patient may decline surgery (e.g. due to development of new co-morbidity, or other reasons). Any occurrence of non-compliance with a recommendation for salvage surgery will be recorded, including the reason. However, based on our experience in Toronto, although sometimes patients may delay recommended surgery (e.g. due to life circumstances or COVID-19 pandemic related reasons), we have not had any patient completely refuse surgery and to date, ultimately all patients who were advised to have surgery by study investigators have done so. In the case of patients who initially decline surgery, close AS follow-up will continue, with imaging and clinical follow-up frequency per discretion of the study investigator (typically 3 to 6 months).

**Table 2 T2:** Definition of disease progression.

Definition of progression of papillary thyroid cancer under active surveillance for which salvage surgery is advised (one or more of the criteria listed below)*
1. Primary index PTC growth >3 mm (in the largest dimension), confirmed on two consecutive ultrasound exams. The 3 mm size cut off is considered reproducible (21)
2. Primary PTC growth in a location that is concerning (e.g. immediately adjacent to the trachea or in the course of the recurrent laryngeal nerve) (22)
3. Incident development of metastatic PTC to lymph nodes (confirmed on cytology or unequivocal imaging)
4. Incident development of distant metastatic PTC (confirmed on imaging or biopsy or surgical histology)

*Patients may choose to have surgery in absence of disease progression at any time point in follow-up.

Thyroid cancer-related medical records will be reviewed by study staff at least yearly, for up to 10 years, regarding thyroid cancer outcomes, treatments, and potential treatment-related complications. Patient questionnaires/interviews and communication scripts are in English for most study sites, but in (Quebec/Canadian) French for Quebec sites.

For patients recruited in the multi-centre study, a baseline self-administered written questionnaire includes demographics and medical history, a question on baseline disease management preference, as well as the following patient-reported outcomes: i) quality of life (thyroid cancer/cancer-specific - EORTC QLQ-THY34 (12) with EORTC QLQ-C30 (13) and ii) anxiety (Generalized Anxiety Disorder Screener, GAD-7) (14). Patients recruited from the original Toronto study who had previously completed a baseline questionnaire as outlined in the original study protocol (10), will not perform a repeat baseline assessment, but relevant original baseline data will be reported.

Yearly follow-up questionnaires (up to 5 years) include: an update of thyroid cancer status and thyroid cancer treatments as well as the following questionnaires: i) quality of life (thyroid cancer/cancer-specific - EORTC QLQ-THY34 (12) with EORTC QLQ-THY34 (13) ii) anxiety (Generalized Anxiety Disorder Screener, GAD-7) (14), iii) survivors’ concerns (Assessment of Survivor Concerns, ASC [1])), and iv) decision regret, relating to the original decision to undergo AS or surgery [decision regret scale (15)]. The questionnaires used in this study to evaluate quality of life and psychosocial outcomes have all been previously used in cancer populations.

For sites in the province of Quebec using French language EORTC QLQ-THY-34 (12) and ASC (16) adapted to Quebec French are not available at the time of initiation of this protocol so they will be initially omitted, with the intention of incorporating them once available (after approval of research ethics board amendments in sites in the province of Quebec).

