For categorial outcomes, we will report proportions with 95% confidence intervals according to AS or surgical group. For all categorical clinical outcomes for which there is a sufficient number of events for meaningful analysis, we will compare the AS and surgical groups using competing risks models. We will summarize the following secondary patient-reported outcomes in each group: i) quality of life (thyroid cancer/cancer-specific) (12, 13), ii) anxiety (14), iii) survivor concerns (16), and iv) decision regret (15) (relating to the original decision on VL-PTC disease management). The data will be reported at last available study follow-up, with data from prior time points analyzed in interim analyses, if there are sufficient patients and events for meaningful analysis. All questionnaire data will be scored as per developers, for total scores or subscale scores. Where patient reported outcomes are missing and patients are known to be alive, multiple imputation will be used, with other outcomes one the same patient at the same time or other times in the imputation model. For each questionnaire outcome, we will calculate summary statistics to characterize the cohort at the last follow-up. Analyses will be adjusted for baseline variables, including age, sex, and primary tumor size (≤ 1cm or > 1cm) as well as duration of follow-up. If sufficient data are available for meaningful analysis will examine predictors of psychosocial health outcomes (e.g. age, sex, primary tumor size) if sufficient data are available for meaningful analysis. Clinical outcomes will also be compared between men and women, if there are sufficient events.

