
Low risk PTC patients’ rationale for AS or surgery is important to understand. Our preliminary findings on patients’ rationale for AS (10) confirmed prior observations reported by D’Agostino et al. at Memorial Sloan Kettering, who reported that some patients perceived the cancer as relatively indolent and experienced concerns related to living without a thyroid or requiring thyroid hormone treatment (19). Concerns about taking thyroid hormone are commonly expressed by patients considering thyroid surgery. A recent international survey of more than 12,000 patients on thyroid hormone treatment suggested prominent dissatisfaction in about 15% of patients taking levothyroxine (20). Although only a small subset of surveyed patients had a history of thyroid cancer (346 patients), thyroid cancer patients reported a high level of agreement with a statement indicating that thyroid hormone treatment impacted their lives (20). The concerns that are expressed by some thyroid cancer patients regarding the long-term implications of thyroidectomy and thyroid hormone treatment are important for healthcare practitioners to acknowledge and formally address in the discussion of disease management choices. However, it is equally important to acknowledge that for some patients, their primary goal in managing their disease is cure of the cancer (by surgery and other treatments, if needed) (10). For informed, low risk PTC patients who are not comfortable living with the knowledge of an untreated thyroid cancer, surgery is clearly the preferred initial disease management choice (10). Appropriate disease management of small, low risk PTC should thus incorporate consideration of patients’ preferences.

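### For multi-centre recruits the survivor-concerns questionnaire (ASC) is not taken at baseline, so a later arm difference cannot be adjusted for the ASC level at entry

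*Protocol article*

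**What the plan says.** All references are to the protocol article.

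- **Baseline** (Study Follow-Up Assessments and Outcomes). Multi-centre recruits report demographics, medical history and a management preference, "as well as the following patient-reported outcomes: i) quality of life (thyroid cancer/cancer-specific - EORTC QLQ-THY34 (12) with EORTC QLQ-C30 (13) and ii) anxiety", the last by GAD-7. The ASC is not on the list.
- **Follow-up** (same section). "Yearly follow-up questionnaires (up to 5 years) include: an update of thyroid cancer status and thyroid cancer treatments", then quality of life and anxiety again, and two instruments not used at baseline: "iii) survivors’ concerns (Assessment of Survivor Concerns, ASC" and the decision regret scale.
- **Toronto patients** (same section). Those who completed the earlier study's baseline form "will not perform a repeat baseline assessment, but relevant original baseline data will be reported". The content of that form is not shown.
- **Quebec** (same section). French-language sites omit the ASC and the QLQ-THY34 until Quebec French versions exist.
- **Analysis** (Statistical Analysis). The secondary patient-reported outcomes summarised by group include "iii) survivor concerns (16), and iv) decision regret (15"). Adjustment is for baseline variables, of which age, sex and tumour size are named, plus length of follow-up.
- **Use of the surgical arm** (Sample Size Calculation). Recruiting it is said to make controlled comparison possible on secondary outcomes.
- **Allocation** (eligibility and recruitment section). "Patients are free to make their own disease management choice".
- **Grounds for the choice** (Discussion). For informed, low-risk "patients who are not comfortable living with the knowledge of an untreated thyroid cancer, surgery is clearly the preferred initial disease management choice". The Introduction adds that surgery choosers in Toronto wanted the cancer out.

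**The concern.** Two instruments appear only at follow-up, and they differ in kind. Decision regret cannot exist before a decision. Concern about the cancer can, because every participant already has cytology read as, or suspicious for, papillary cancer at entry.

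The arms are self-selected, and the document ties the selection to how patients feel about leaving a cancer untreated. If surgery choosers enter with more concern, a difference in ASC at years 1 to 5 mixes who chose what with what the choice did. Relief after surgery could be hidden, or AS could look more reassuring than it is. This matters because the Discussion names patient counselling as a use of the results.

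This is a gap in data collection. For GAD-7 and the EORTC forms, a baseline score can be brought into the analysis later. For the ASC itself, no analysis plan can supply a score that was not taken.

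**Working it through.** **1. The schedule.** The claim rests on two lists in one section.

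| Instrument | Baseline (multi-centre) | Yearly follow-up | Could be asked before the choice? |
|---|---|---|---|
| EORTC quality of life | yes | yes | yes |
| GAD-7 | yes | yes | yes |
| ASC | no | yes | yes, perhaps with an instruction line |
| Decision regret | no | yes | no |

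The ASC is the only outcome that could be taken beforehand and is not. That its first administration falls about one year in is inferred from the yearly schedule; the anchor date is not stated.

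**2. How many patients.** The planned total is 450. The Toronto study recruited 200, of whom those consenting to long-term follow-up are included. If all 200 are, they make up 200/450 = 44%, and 450 − 200 = 250 patients fall under the multi-centre baseline list. If fewer are, that number is larger.

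**3. The plan's own figure.** The plan gives none for the ASC. Its one calculation, 328 AS patients for an expected 95% interval half-width of 2% around 3%, comes out at 327 with exact binomial intervals. It does not bear on this point.

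**4. Illustration of size.** The documents give no ASC standard deviation, entry gap or correlation, so all of these are assumed.

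- Entry gap between arms: d = 0.3 SD (range 0.2 to 0.5).
- Correlation of baseline with follow-up ASC: r = 0.5 (range 0.3 to 0.7).
- True effect of management on the ASC: none.
- Arm sizes: 330 and 120, the plan's expected numbers.

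Carry-over into the follow-up contrast = d × r = 0.3 × 0.5 = **0.15 SD**. Range: 0.2 × 0.3 = 0.06 to 0.5 × 0.7 = 0.35 SD.

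Standard error = √(1/330 + 1/120) = √0.01136 = **0.107 SD**.

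If a two-sided 5% test were run, 0.15/0.1066 = 1.407, and P(|Z + 1.407| > 1.96) = **29%** (9% to 91% over the ranges).

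With fewer ASC respondents, say 250 and 90, the standard error is √(1/250 + 1/90) = 0.123. The ratio is then 0.15/0.123 = 1.22 and the rate about 23%. The carry-over itself does not change.

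**5. With a baseline ASC in the model.** Under the same linear model, in which the entry difference acts only through the baseline score, the carry-over is removed. The standard error becomes 0.1066 × √(1 − r²) = 0.1066 × √0.75 = 0.092 (0.102 at r = 0.3, 0.076 at r = 0.7).

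**The case against.** Several objections stand, and they bound the point.

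- **A reader might infer that no patient in the study has a baseline ASC.** The closed list covers multi-centre recruits only. The Toronto form is not shown, so nothing can be said about those patients.
- **A reader might infer that the arms are known to differ in worry and that worry drove the choice.** The documents report no measured difference. The Introduction describes a goal, removal of the cancer, and the Discussion makes a counselling statement. They make an entry difference plausible and give no size.
- **A reader might infer that nothing can be done without a baseline ASC.** Baseline GAD-7, QLQ-THY34, QLQ-C30 and stated preference are collected, and the covariate list is worded as open. But GAD-7 measures general anxiety, QLQ-THY34 is initially missing at French-language Quebec sites, and none of these is named as a covariate. They give partial control.
- **A reader might take 29% as the plan's error rate.** No significance test of the ASC is specified; the wording is mostly about summaries by group. The rate is conditional on a test that the plan does not state and on inputs that it does not give.
- **A survivorship form may have been kept for follow-up on purpose.** Its items are not shown, so this is possible. However, the plan already gives it yearly to AS patients whose cancer is untreated, so it accepts the form in that state.
- **Non-randomisation is already admitted as a limitation.** It is, but that is no reason to leave a measurable source of confounding unmeasured.

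**Conclusion.** The point holds for multi-centre recruits: the ASC is a secondary outcome reported by self-selected arm, with no baseline score and no named covariate that stands in for one. Whether this distorts the contrast depends on an entry difference that the documents make plausible but do not measure. The 0.15 SD figure, and its range of 0.06 to 0.35 SD, show what such a difference could do; they do not estimate what it will do.

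The primary failure rate is untouched, and one of four secondary patient-reported outcomes is affected. This is an inexpensive improvement, worth making while recruitment is open because each patient enrolled before the change lacks the baseline score for good.

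**What to change.** 1. **Patients still to be recruited.** Add the ASC to the baseline questionnaire, with an instruction line if any items presuppose treatment, and at Quebec sites once the French form is available. Have it completed before the management choice is recorded where possible; the article does not say whether the baseline questionnaire precedes the choice. Adjust the ASC comparison for this score.
2. **Patients without a baseline ASC**, including Toronto patients unless their original form held it. Adjust for the baseline patient-reported scores that exist, and report the ASC arm contrast as descriptive, without attributing it to AS or surgery.
3. **Wording.** State that adjustment reduces confounding by choice and does not remove it. Some patients refer themselves already wanting AS.

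The cost is slightly more burden at baseline from a form already in the follow-up set, and an ethics amendment. The ASC analysis will also have to handle two groups of patients, with and without the baseline score.
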